#### Antibiotics

For the choice and duration of antibiotics the practice guidelines of the Dutch Antibiotic Policy Committee [28] and the American Society of Colon and Rectal Surgeons [30] are followed. In both guidelines, a minimum of 7-14 days of broad-spectrum antibiotics is advised. In the present study amoxicillin-clavulanic acid is chosen as broad-spectrum antibiotic; duration of antibiotic treatment is 10 days. The dosage scheme for the study drug is 1200 mg i.v. 4 times daily with subsequent oral administration of 625 mg 3 times daily. In case of allergy (known or newly diagnosed), a switch will be made to the combination of ciprofloxacine and metronidazole; ciprofloxacine 2 times a day 400 mg i.v. and metronidazol 3 times daily 500 mg, with oral doses of ciprofloxacine being 500 mg 2 times a day and of metronidazol 3 times a day 500 mg.

### Endpoints

The primary endpoint is time-to-full recovery within a follow-up period of 6 months. Full recovery is defined by the following criteria: discharged from the hospital (out-patient), normal diet (defined by tolerating solid food and more than 1L of fluid orally), temperature < 38.0°C, and VAS pain score < 4, no use of daily pain medication or back to pre-illness pain medication use, and resuming to pre-illness working activities; as assessed by questionnaires and out-patient clinic visits.

The secondary endpoints are: proportion of patients who develop complicated diverticulitis require surgery or non-surgical intervention; number of days outside the hospital in a 6 months period; direct and indirect medical costs at 6 months follow-up; occurrence of complicated diverticulitis defined as abscess, perforation, stricture and/or fistula; predefined side-effects of initial antibiotic treatment (e.g. antibiotic resistance/sensitivity pattern, allergy); morbidity (e.g. pneumonia, myocardial infarction, urinary tract infection); mortality; readmission rate within 6 months and acute diverticulitis recurrence rates at 12 and 24 months follow-up. Changes in health status and valuation over time will be measured using generic and disease specific quality of life questionnaires (Euro-Qol 5D, Short Form 36 (SF-36) and the Gastro-Intestinal Quality of Life Index (Giqli)) on admission and after 3, 6, 12 and 24 months.

A recurrence is defined as ultrasound- or CT-proven acute diverticulitis after complete resolution of symptoms more than 1 month after initial discharge from hospital. If a patient dies during follow-up, the reason for death will be recorded as related or unrelated to diverticular disease.

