### Study outline

Patients will be randomly allocated to one of the following two treatment strategies: Conservative strategy including immediate antibiotic treatment or liberal strategy without antibiotics (supportive measures only). (Table 4).

**Table 4 T4:** Treatment strategies

Conservative strategy with antibiotics	Liberal strategy without antibiotics
- Hospital admission;	- Admission only if discharge criteria are not met;

- Intravenous fluids and at least 48 hours of intravenous antibiotics and subsequently switch to oral antibiotics if tolerated (otherwise continuation i.v.) to complete a full 10-day treatment duration;	- No initial antibiotics;

- Adequate pain relief (VAS < 4);	- Adequate pain relief (VAS < 4);

- Oral intake as tolerated;	- Oral intake as tolerated;

- Daily monitoring.	- Daily monitoring when admitted to the hospital;

-Self monitoring at home after discharge -Out patient follow-up at regular intervals	- Self monitoring at home. - Out patient follow-up at regular intervals

In the conservative strategy, the use of antibiotics will be intravenously for at least 48 hours after which route of administration can be switched to orally if tolerated. Hospital admission in the liberal strategy is needed for patients with nausea and vomiting, in need of intravenous fluids or for patients with excessive pain not properly reacting to oral pain medication.

The interval between start of symptoms of the patient and administration of antibiotics will be registered. Also the period after inclusion and the actual first administration of antibiotics will be registered.

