In both strategies CT is repeated in case of clinical deterioration. For patients in the liberal strategy treatment arm, clinical deterioration and/or proven subsequent complicated diverticulitis and/or other infectious foci (e.g., pneumonia, infections) may dictate start of antibiotic treatment, instigated by the treating physician. Criteria to start antibiotics in the liberal arm are temperature > 39°C, positive blood cultures and clinical suspicion of bacteraemia (i.e. sepsis). Criteria for sepsis are set by the American College of Chest Physicians and the Society of Critical Care Medicine. Two or more symptoms are required: Body temperature < 36°C or > 38°C, heart rate higher than 100 beats a minute, respiratory rate higher than 20 breaths a minute and white blood cell count < 4 × 10^9 ^or > 12 × 10^9 ^cells/L [31]. Also another infectious focus (e.g., pneumonia, urinary tract infections) may dictate start of antibiotic treatment, instigated by the treating physician.

The following discharge criteria are applied in both strategies: normal diet (defined by tolerating solid food and more than 1L of fluid orally), temperature < 38.0°C, VAS (Visual Analoge Score) pain score < 4 (with paracetamol only), self support as compared to the pre-illness level, and acceptance by the patient.

All outpatients will daily monitor and register their body temperature. Written and oral instructions at discharge are given, and relevant telephone numbers and contact information will be provided. In case of fever above 38˚C, progression of pain above a VAS of 4 or other clinical signs of deterioration, patients can contact the hospital or emergency department immediately.

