### Sample size calculation and date analysis

A non-inferiority design was chosen. Time-to-full recovery in the liberal strategy arm must not exceed a clinically relevant difference of more than 5 days compared with the conservative strategy. When this condition is fulfilled, the potential advantages of the liberal (non-antibiotic) strategy become dominant: patient well being when the need of hospital admission can be avoided, less costs, less antibiotic resistance and less other side effects. The study must have the power (superiority) to detect a difference in time-to-full recovery of 5 days.

The median time-to-full recovery is 21 days based on the National Dutch Hospital Registry data with an average of 7 days admission and an assumed additional median 14-day out-patient period to full recovery. To reject the null-hypothesis of a difference in time-to-full recovery of 5 days or less, using a time-to-event analysis with a power of 85% at a confidence level of 95%, an accrual period of 730 days and a follow-up period of 180 days, at least 264 patients need to be included in each treatment arm. With an estimated one percent of the trial patients lost to follow-up, a total 533 patients is needed.

The primary endpoint is time-to-full recovery. Kaplan-Meier curves depicting the proportion of patients with full recovery since randomisation will be constructed for both strategies. The log rank test will be used to test for superiority of one strategy compared with the other. Testing for non-inferiority will be done by calculating the hazard ratio for the liberal strategy compared with the conservative strategy using Cox regression. We will calculate a one-sided 95% confidence interval for this ratio to determine whether it reaches outside the hazard ratio belonging to an equivalence limit of a difference of 5 days in median survival time.

For other endpoints data will be compared by the Student's t test, Wilcoxon rank sum test, Chi square test or Fischer exact test as appropriate. In superiority tests a two-tailed P value ≤ 0.05 will be considered statistically significant, whereas one-sided tests will be performed in non-inferiority testing. The main analyses will be based on the intention to treat principle. Predefined subgroup analyses to investigate whether treatment effects are different in subgroups will be performed for Hinchey classification 1a versus 1b and for participating center.

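### The antibiotic side-effect endpoint is limited to initial treatment, so it omits harms of antibiotics started later and overstates the liberal arm's advantage

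*Protocol article*

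**What the plan says.** All references are to the protocol article.

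- **Endpoints.** The list of secondary endpoints includes "predefined side-effects of initial antibiotic treatment (e.g. antibiotic resistance/sensitivity pattern, allergy"). No other listed endpoint is specific to antibiotic harm.
- **Study outline and Table 4.** The randomised options are "Conservative strategy including immediate antibiotic treatment or liberal strategy without antibiotics (supportive measures only"). Table 4 describes the liberal arm with "No initial antibiotics". The Objective section describes that strategy with the same adjective.
- **Study outline, later antibiotics.** In the liberal arm, deterioration, proven complicated disease or another infectious focus "may dictate start of antibiotic treatment, instigated by the treating physician". Criteria for starting are listed there. No expected proportion of patients is given.
- **Sample size and data analysis.** For secondary endpoints: "For other endpoints data will be compared by the Student's t test, Wilcoxon rank sum test, Chi square test or Fischer exact test as appropriate". The threshold is stated as "In superiority tests a two-tailed P value ≤ 0.05 will be considered statistically significant", and the analysis set as "The main analyses will be based on the intention to treat principle". The same section names, among the advantages that count once non-inferiority is met, "less costs, less antibiotic resistance and less other side effects".
- **Safety monitoring and Cost analysis.** All adverse events are recorded, whether or not thought related to the study drug. Medication used is collected for costing.

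**The concern.** The adjective that limits the endpoint is the one that defines what the liberal arm does not receive. Read together, the two passages leave a liberal patient almost no way of contributing an event, short of being given immediate antibiotics against the allocation. Allergy, resistance or antibiotic-associated diarrhoea after a later course is a consequence of the allocated strategy, but it is not counted.

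This matters because the trial is presented as a pragmatic comparison of two strategies, analysed as randomised. The relevant quantity is then the antibiotic harm that each strategy produces, later courses included. Fewer side effects and less resistance are also part of the stated case for preferring the liberal strategy once non-inferiority is shown. With the present wording, the endpoint that should measure that advantage partly fixes it in advance. The distortion grows with the share of liberal patients who end up needing antibiotics.

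**Working it through.** The plan gives no figure for this endpoint, so there is none to reproduce. The check has two parts: what the wording counts, and how much that could matter.

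**1. What is counted**

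| Antibiotic course | Conservative arm | Liberal arm |
|---|---|---|
| Initial course | given to all, counted | not given |
| Later course | possible, not counted | permitted, not counted |

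Later courses are left out in both arms, but only the liberal arm is left with nothing to count. No other section extends the endpoint to later courses.

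**2. Size**

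Inputs:
- n = 264 per arm (sample size section).
- h = harm rate per treated patient. The Background gives toxicodermia of 7-8% with amoxicillin; the midpoint of 7.5% is used. It also gives 1% for allergic reactions, used as a second case. The two are not added, because the article does not say whether they overlap.
- r = share of liberal patients who receive later antibiotics. This is **not stated; 5-30% is assumed**.
- The same h is assumed for later courses, and later courses in the conservative arm are set to zero.

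Formulas:
- Conservative events = n × h
- Liberal events, as worded = 0 for any r
- Liberal events, any antibiotic = n × r × h
- Difference, as worded = h; any antibiotic = h × (1 − r)
- Overstatement = h × r in absolute terms, or a ratio of 1/(1 − r)

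With h = 7.5%, conservative events are 264 × 0.075 = 19.8, and the difference as worded is 7.5 points.

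| r | Liberal events not counted | Difference, any antibiotic | Overstatement | Ratio |
|---|---|---|---|---|
| 5% | 264 × 0.05 × 0.075 = 1.0 | 7.1 points | 0.4 points | 1.05 |
| 10% | 2.0 | 6.75 points | 0.75 points | 1.11 |
| 20% | 4.0 | 6.0 points | 1.5 points | 1.25 |
| 30% | 5.9 | 5.25 points | 2.25 points | 1.43 |

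With h = 1%, there are 2.6 conservative events, against 0 as worded and 0.1-0.8 (r = 5-30%) when any antibiotic counts.

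**3. Would the conclusion change?** At h = 7.5% and r = 30%, the rounded counts are 20 versus 6 of 264, for which Fisher's exact test gives p of about 0.008. At h = 1%, even the comparison as worded (3 versus 0) gives p of about 0.25. In these cases the wording changes the size of the contrast and not its direction or its significance.

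**4. Why this is an upper bound.** If a share s of conservative patients has a further course at the same harm rate, the overstatement falls to roughly h × (r − s), which is below h × r whenever s is above zero.

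**The case against.** The strongest reply has four parts.

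*The article is a condensation.* It gives examples only, and the predefined list and counting window may stand in the full protocol. Resistance patterns could be assessed in either arm, and the Discussion speaks of Clostridium-associated diarrhoea as a topic of the study without limiting it to an initial course. This is fair as to detail, and it is a reason to write that the liberal arm can hardly contribute events, not that it never can. But the limit to initial treatment is something the article states, not something it leaves out. If the word was meant as treatment of the initial episode, that departs from its use in Table 4 and the Objective section and would still omit antibiotics for other infections.

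*The harms are not lost.* A reader might infer that side effects of later antibiotics go unrecorded. The documents do not support that: all adverse events are recorded in both arms, morbidity is a separate endpoint, and medication enters the costs. What is lost is their place in the one predefined antibiotic-harm endpoint.

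*The advantage comes from the allocation.* A reader might infer that the wording creates the liberal arm's advantage. It does not. One arm receives a 10-day course by design and the other does not, so fewer side effects would be expected under any sensible definition. The sentence on advantages is a rationale for the non-inferiority design and not a decision rule that uses this endpoint. The article also lists its secondary tests generically and does not single this endpoint out.

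*The numbers are soft.* This stands. No rescue share is given. The Background says that less than 10% need percutaneous or operative treatment, but that is not a rate of antibiotic use and lends no support to the top of the assumed range.

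**Conclusion.** The point holds in a limited form. As worded, the endpoint excludes side effects of later antibiotics, and the liberal arm is defined by having no initial ones. A comparison by randomised arm therefore sets the conservative rate against something close to a structural zero and overstates the liberal strategy's advantage.

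On the assumptions of 5-30% later antibiotic use and a 7.5% harm rate, about 1-6 liberal-arm events per 264 go uncounted and the difference is inflated by at most about 0.4-2.3 percentage points. The omission applies to later conservative-arm courses as well, so it is not strictly one-sided. It concerns one secondary endpoint, leaves the primary non-inferiority test untouched, and would probably not reverse the direction of the result. It is worth correcting because the inflated quantity is one of the stated reasons for preferring the liberal strategy.

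**What to change.** Reword the endpoint as predefined side effects of **any** antibiotic given from randomisation to 6 months, whatever the indication, in both arms and analysed by randomised arm. Report beside it, per arm, the proportion of patients receiving any antibiotic and the total antibiotic days. Side effects of the initial course can stay as a descriptive line for the conservative arm.

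The cost is small. It is a change of endpoint wording that alters no treatment rule, and adverse events and medication use are already to be collected. The predefined list has to be applied to later courses in the same way as to the first. The downside is that the liberal arm's apparent side-effect advantage becomes somewhat smaller.

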**Conclusion:**

A clinically relevant difference of more than 5 days in time-to-full recovery between the two treatment strategies is not expected. The liberal strategy without antibiotics and without the strict requirement for hospital admission is anticipated to be more a more cost-effective approach.

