### Cost analysis

All related costs will be estimated based on the actual input terms of resource use and personnel in the 6-month follow-up period after randomization. For all cost-items such as hospital admission, medication used, diagnostic tests, unit costs will be derived from the Dutch costing manual or determined in cooperation with the hospital administration. Direct medical costs will be recorded in the case record forms. Indirect costs arising from losses in productivity will be assessed by means of the Health and Labor questionnaire and will be calculated by means of the friction cost method.

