### Economic evaluation

The economic evaluation will be performed from a societal perspective as a cost-effectiveness and cost-utility analysis. The main analyses include costs per day reduction to achieve full recovery and costs per QALY gained. Additional sensitivity analyses, regarding differences in possible subgroups, will be performed.

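### With no EQ-5D between admission and 3 months, the cost-per-QALY analysis loses from about half to nearly all of a 5-day difference in recovery

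*Protocol article*

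**What the plan says.** Under Endpoints, the EQ-5D, SF-36 and GIQLI share one timetable: "on admission and after 3, 6, 12 and 24 months". Their stated purpose covers health status and its valuation: "Changes in health status and valuation over time will be measured using generic and disease specific quality of life questionnaires".

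Under Economic evaluation: "The main analyses include costs per day reduction to achieve full recovery and costs per QALY gained". Under Cost analysis, costs are counted "in the 6-month follow-up period after randomization".

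Under Sample size calculation and date analysis: "The median time-to-full recovery is 21 days". The non-inferiority limit is "an equivalence limit of a difference of 5 days in median survival time".

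The article does not state how utility between two measurements is derived.

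**The concern.** A QALY is the area under a utility curve. In this illness the curve should move mainly in the first weeks, since half the patients are expected to have recovered by day 21. The timetable has one point at the start and the next at about day 91, when most patients in either arm are expected to be well. A difference in speed of recovery then reaches the QALY estimate mainly through the few patients still unwell at 3 months. What happens in between has to be filled in by assumption.

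This affects one of the two main economic results in a trial whose title question is cost-effectiveness. An analysis plan can choose a better interpolation rule, but it cannot supply utilities that were never measured. SF-36-derived utilities would not help, because they follow the same timetable.

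**Working it through.** The article gives no QALY figure to reproduce, so this is a check of what the timetable can capture.

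**Inputs from the article.** Median recovery is 21 days and the margin is 5 days in the median, so the comparison is 21 versus 26 days. Utilities are measured at entry, 3 and 6 months (days 0, 91, 182). Costs run over 6 months.

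**Assumptions not in the article.** Utility is reduced by a constant 0.3 until recovery, then returns to normal. Values between measurements lie on a straight line. The QALY horizon is 6 months, like the costs. The percentages captured do not depend on the 0.3, which cancels.

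**Formulas.** The proportion unrecovered at day t is S(t) = 0.5^((t/m)^k), with median m and shape k (k = 1 is exponential).
- True illness-days: the integral of S from 0 to 182.
- Planned timetable: 45.5 × [1 + S(91)] + 45.5 × [S(91) + S(182)].
- With days 14 and 28 added: 7 × [1 + S(14)] + 7 × [S(14) + S(28)] + 31.5 × [S(28) + S(91)] + 45.5 × [S(91) + S(182)].
- QALY loss: 0.3 × illness-days / 365.25.

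**Exponential case in full.** S(91) is 0.0496 (median 21) and 0.0884 (median 26); S(182) is 0.0025 and 0.0078.
- True illness-days: 30.22 and 37.22, a difference of 7.00.
- Planned timetable: 45.5 × 1.1017 = 50.13 and 45.5 × 1.1846 = 53.90, a difference of 3.77. Captured: 3.77 / 7.00 = 54%.
- In QALYs: true 0.3 × 7.00 / 365.25 = 0.00575, measured 0.0031.
- Overstatement in the 21-day arm: 50.13 / 30.22 = 1.66, or 66%.

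**All three shapes** (illness-days for medians 21 / 26; differences taken before rounding):

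| | Exponential | Weibull 1.5 | Weibull 2 |
|---|---|---|---|
| Unrecovered at day 91 | 5.0% / 8.8% | 0.2% / 1.1% | about 0% / 0% |
| True | 30.22 / 37.22 | 24.21 / 29.97 | 22.35 / 27.68 |
| True difference | 7.00 | 5.76 | 5.32 |
| Days 0, 91, 182 | 50.13 / 53.90 | 45.68 / 46.47 | 45.50 / 45.52 |
| Difference seen | 3.77 (54%) | 0.80 (14%) | 0.02 (under 1%) |
| Overstatement, 21-day arm | 66% | 89% | 104% |
| With days 14 and 28 | 35.03 / 42.05 | 29.99 / 36.21 | 28.52 / 35.70 |
| Difference seen | 7.02 (100%) | 6.22 (108%) | 7.18 (135%) |
| Overstatement, 21-day arm | 16% | 24% | 28% |

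At a loss of 0.3, the true QALY differences are 0.00575, 0.0047 and 0.0044; the planned timetable shows 0.0031, 0.0007 and 0.00002.

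**Other curves.** Log-normal recovery with sigma 1.0, 0.75 and 0.5 gives 50%, 33% and 7% captured on the planned timetable. The exponential curve is the most favourable of those tried.

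**The case against.** Several points on the other side have force.

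- **Interpolation is not stated.** A fuller plan could use each patient's recovery date, which is the primary endpoint, to place the change in utility. This stands: the straight line is this review's assumption. But such a plan would have to assume how utility runs up to that date, because none is measured there.
- **The schedule is not blind.** A reader might infer that the QALY analysis cannot see the recovery difference at all. The 54% under exponential recovery contradicts that. Slow recoverers and later complications are still picked up at 3 and 6 months.
- **The economic question does not rest on QALYs alone.** A reader might infer that the trial cannot answer its cost-effectiveness question. The Objective section ties cost-effectiveness to time to full recovery, which is measured without EQ-5D.
- **The amount is small.** What is missed is 0.00575 − 0.0031 = about 0.0027 QALY (exponential) to about 0.0044 (shape 2). At an assumed 20,000 to 80,000 euros per QALY, that is roughly 50 to 350 euros per patient. Nothing here shows that the economic conclusion would change.
- **The remedy is not exact.** A figure of 135% is an overstatement of the difference. It is still much closer than under 1% for the same curve.

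Three further readings are tempting but not supported. The article does not say that the expected difference in recovery is about zero, which would make cost per day unstable; the Abstract says only that "A clinically relevant difference of more than 5 days in time-to-full recovery between the two treatment strategies is not expected". The baseline timing most naturally means study entry for every patient, including those managed at home. Silence on bootstrap or net-benefit methods is normal for an article.

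**Conclusion.** The point holds as a weakness in the utility timetable. The assessment times are fixed in the article and are poorly matched to its own 21-day median and its own choice of cost per QALY as a main analysis. For a 5-day difference in medians, the planned times capture between about half and almost none of the QALY difference. They overstate the loss per patient in the 21-day arm by about 65-105% under the exponential and Weibull curves.

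The range reflects the unknown shape of the recovery curve. The size rests on a constant utility loss until recovery, straight-line interpolation and a 6-month horizon, none of which the article states. The primary endpoint, the non-inferiority conclusion and the recovery-based economic result are not affected. This is a cheap improvement worth making, not a flaw that defeats the trial.

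**What to change.** Add the EQ-5D alone (five items) at about 2 and 4 weeks after randomisation in both arms, alongside the questionnaires and out-patient visits already used to assess recovery. Leave the SF-36 and GIQLI as scheduled. State the added times in the Endpoints section.

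The cost is two short questionnaires per patient, which is slightly more burden, with no new procedures. The change must be made before enrolment starts.
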